#### Automated Caries Scoring System

The automated caries scoring system will be applied to the occlusal surfaces of primary teeth and visualized using the commercially available software (TPM version 2.3; 3Shape TRIOS A/S) on a laptop with a 15-inch monitor (Alienware, DELL). Using a predefined logistic regression function, this software identifies a healthy reference standard per tooth and compares regions of interest to the healthy reference, to quantify fluorescence changes [16]. The automated system classifies a region of interest as caries based on the predefined cut offs which have been validated using permanent tooth histology as a reference standard, to indicate relative caries depth. The software classifies a surface as sound, initial caries (ICDAS 01/02) or moderate-extensive caries (ICDAS>03), and this is indicated on the 3D models as a yellow or red overlay respectively (Figure 1). The automated classification will be recorded using REDCap.

### Sample Size

This is a retrospective study drawing all eligible participants from the MISBAIR trial who underwent the dental assessment at their 5-year-old study visit.

### Outcome Measures

For agreement analyses, ICDAS and modified ICDAS codes will be collapsed for each surface into four categories labeled sound surface (0), initial caries (1), moderate (2), and extensive caries (3). A binary dental caries variable will be created for each surface, and the detection threshold will be initial caries (0 vs 1, 2, and 3).

### Statistical Analysis

Data checking and cleaning will take place before analysis. Descriptive statistics for patient characteristics such as age, sex, caries prevalence, and the proportion of children with enamel defects will be reported. The total number of tooth sites included in the analysis will be reported.

Descriptive characteristics for the rater population will be reported, including qualification, clinical background, years of experience, and training results for each rater. Interrater and intrarater reliability for on-screen assessment of 3D models based on color and fluorescence using the intraclass correlation coefficient will be reported for all examiners. These estimates will be obtained from a multilevel model fitted to the surface-level data, accounting clustering (see below), and zero inflation.

To assess agreement among methods, we will undertake both surface-level and individual-level analyses. At the surface level, caries data naturally have 3 levels with surfaces clustered within a tooth, which are clustered within an individual. Therefore, for this analysis, we will use multilevel logistic regression to estimate method agreement while accounting for clustering for the tooth. Specifically, separate multilevel models will be fitted to compare VE with each of the alternative methods by including the variable method (VE vs on-screen assessment of 3D models in approximate natural colors, on-screen assessment of 3D models in approximate natural colors featuring fluorescence, and automated system) as the fixed effect. The coefficient estimates for the variable method will be used to indicate the level of agreement. The multilevel model will be fitted with a zero-inflated binomial distribution.

At the individual level, a numerical variable representing the number of lesions per individual will be generated and analyzed with 2 approaches. First, Bland-Altman method agreement analysis will be performed using a regression approach. Specifically, a model will be constructed to regress the difference between each pair of methods on their average [36]. The analysis will be repeated for each possible pair of methods. Second, for each possible pair of methods, an intraclass correlation coefficient will be estimated from a multilevel model fitted to the paired data consisting of the 2 measures for each individual obtained from the 2 methods, fitted with a zero-inflated Poisson distribution.

A sensitivity analysis will explore the impact of the diagnostic threshold used on agreement estimates. Analyses will be repeated with the caries data dichotomized at alternative thresholds: the moderate and extensive thresholds. In the analysis of the moderate threshold, sound and initial surfaces will be labeled caries absent (0) and all remaining categories (moderate-extensive) will be labeled caries present (1). In the analysis of the extensive threshold, sound, initial, and moderate caries will be combined and labeled as caries absent (0) and only teeth with extensive caries will be marked as caries present (1). To evaluate if the surface location and presence of enamel defects impact the diagnostic agreement estimates, these variables will be included as additional variables in the regression models for the surface-level analyses, including interaction terms with the method. The surface location variable will have 3 levels for each visible tooth surface (occlusal, smooth, and proximal). Enamel defects will be a binary variable, defined as present or absent per person. The sensitivity analysis to compare the agreement between on-screen assessment of 3D models in approximate natural colors and on-screen assessment of 3D models in approximate natural colors featuring fluorescence will include additional variables, rater and timing, as fixed effects.

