### Study Design

This is a diagnostic agreement study, as VE is not considered a gold standard in this setting [23]. Dental caries in this study is defined as primary coronal caries. Data sources (age at dental visit, sex, VE data, and 3D models) will be retrospectively sourced from a sample of children who underwent VE using the ICDAS and intraoral scanning with the TRIOS 4 to produce 3D digital models.

The 3D models for each eligible participant will be subject to an on-screen assessment by 4 qualified dental practitioners. Each practitioner will examine all 3D models at 2 separate time points. An on-screen assessment of 3D models based on tissue geometry and approximate natural colors (excitation to visible white light) will take place first (Figure 1A), followed by an on-screen assessment with the addition of fluorescence texture (excitation to light at 415 nm; Figure 1B). An interval of at least 4 weeks will follow to minimize recall bias before the on-screen assessment process is replicated. Occlusal surfaces of primary molars will be examined using the automated caries scoring system at a single time point only (Figure 1C). Examiners will be blinded to all clinical examination data and automated caries scores when scoring the 3D scans.

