A total of 4 examiners will undertake on-screen assessment. Before commencing on-screen assessment, all examiners will undergo a 2-hour training workshop followed by calibration exercises. Training will focus on applying a merged and modified ICDAS criteria to a data set of 3D models with fluorescence. A dentist and expert in using modified ICDAS to interpret 3D models (SM) will facilitate training. To establish interrater agreement, each examiner will independently undertake an on-screen assessment of a training-calibration data set of 200 examination sites. This data set includes carious lesions and sound surfaces which have been validated histologically as part of a previous study [16,20]. Examiners will repeat this calibration exercise 2 weeks after the initial assessment to establish an intrarater agreement. Examiners will repeat the calibration process until the agreement exceeds κ_w_>0.7.

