## Discussion

This protocol aims to fill a knowledge gap by describing an approach for determining the diagnostic agreement between VE using ICDAS and on-screen assessment of 3D models featuring fluorescence obtained with an IOS.

Intraoral scanning is increasingly being adopted in dentistry as it offers improved clinical workflows for patient assessment and treatment planning, particularly in the disciplines of prosthodontics, orthodontics, and periodontics [13,38,39]. The role of scanning technology in supporting clinical diagnostics is an emerging research area [19,20,40-43]. There is paucity in the literature describing on-screen assessment of 3D models as a method for caries detection.

A strength of our study is the consideration of different approaches to analyze agreement. Our use of multilevel generalized linear regression models to analyze surface-level dental caries data has several strengths. First, caries from the same individual are more correlated than those between individuals. If this clustering is ignored, the estimated variance may be misleadingly small [44]. We will use multilevel models that account for clustering. Second, the multilevel regression approach allows for estimating method agreement while accounting for variability due to the influence of the rater and timing of assessment [45]. Finally, because all eligible primary teeth surfaces will be analyzed the high proportion of sound surfaces will result in zero-inflated outcome data. We will address this by fitting a generalized linear regression framework allowing the use of a zero-inflated binomial distribution; whereas traditional agreement methods, such as the κ statistic, are limited in this context [46]. A limitation of the statistical approach is that the coefficient estimates derived from the multilevel model do not quantify absolute agreement. As an alternative analysis, we will analyze the total caries at the individual level with a regression-based Bland-Altman agreement analysis [36]. The excess of zeros and, hence, the nonnormal distribution of the data precludes the calculation of the limit of agreement estimates that are clinically interpretable. Consequently, we will use the intraclass correlation coefficient derived from a multilevel model fitted with a zero-inflated Poisson distribution, acknowledging that this is influenced by the variability in the population.

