Further limitations include the retrospective study design, as multiple raters did not undertake VE over multiple time points, so we cannot account for the effects of this in the analysis. The prospective design of the onscreen assessment is a strength, as it has been designed to capture these effects.

The study results will inform whether 3D models can be used interchangeably with VE for detecting and classifying dental caries. This work serves as a proof of concept for performing dental examinations digitally. Study outcomes may change existing practices for data collection in children for epidemiological research. The findings may also provide insight into how scanners can be used more broadly in the provision of teledentistry services and to improve the access of young children to comprehensive dental examinations.

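### The VE-versus-on-screen models name no surface, rater or time term, although each surface has 8 on-screen readings against one visual examination

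*Protocol article*

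**What the plan says.** Under Study Design, on the four on-screen examiners: "Each practitioner will examine all 3D models at 2 separate time points". Both on-screen methods (colour, and colour with fluorescence) are read this way.

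Under Statistical Analysis, the surface-level plan is stated as: "we will use multilevel logistic regression to estimate method agreement while accounting for clustering for the tooth". Separate models compare VE with each alternative, with method as the fixed effect. The hierarchy described there runs from surface to tooth to individual; there is no level for repeated readings of one surface. Later in the same section, the sensitivity analysis comparing colour with fluorescence "will include additional variables, rater and timing, as fixed effects". That analysis does not involve VE.

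The Discussion lists as a strength that the multilevel approach "allows for estimating method agreement while accounting for variability due to the influence of the rater and timing of assessment".

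At individual level, the intraclass correlation comes from a zero-inflated Poisson model fitted to "paired data consisting of the 2 measures for each individual obtained from the 2 methods".

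**The concern.** The comparison of VE with on-screen reading is central to the first objective. As described, its model does not recognise that the VE reading and the on-screen readings concern the same surface, or that the on-screen readings come from four people on two occasions. The first omission misstates the precision of the method effect. The second matters because the Discussion wants to say whether 3D models are interchangeable with VE and may change epidemiological practice, which is a statement about on-screen examiners in general. A shift produced by these four raters' thresholds could be reported as a property of the method. At individual level the result depends on an unstated reduction of 8 counts to one.

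**Working it through.** **Inputs from the document**
- On-screen raters: "A total of 4 examiners will undertake on-screen assessment". With 2 time points each, 4 x 2 = 8 readings per surface per on-screen method.
- VE: the Discussion says "multiple raters did not undertake VE over multiple time points, so we cannot account for the effects of this in the analysis", so VE is taken as one reading per surface.
- Automated score: "Occlusal surfaces of primary molars will be examined using the automated caries scoring system at a single time point only", so that comparison is 1:1.
- The article states no precision target, interval or rater variance, so there is no planned figure to reproduce. All correlations and variance components below are assumptions.

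**Step 1: repeated readings alone, if stacked.** Take the contrast (mean of 8 on-screen readings minus one VE reading) for a surface, in units of within-tooth variance. Let rho_w be the correlation among on-screen readings of a surface and rho_b the correlation between VE and on-screen.
- Variance assumed by a model with no surface term: 1 + 1/8 = 1.125.
- True variance: 1 + (1 + 7 rho_w)/8 - 2 rho_b.
- Ratio of true to model standard error: sqrt(true/1.125).

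At rho_w = 0.7:

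| rho_b | true variance | SE ratio |
|---|---|---|
| 0 | 1.7375 | 1.24 |
| 0.3 | 1.1375 | 1.01 |
| 0.5 | 0.7375 | 0.81 |
| 0.7 | 0.3375 | 0.55 |

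A ratio above 1 means the interval is too narrow; below 1, too wide. Break-even is rho_b = (7/16) rho_w, which is 0.31 at rho_w = 0.7. The ceiling, at rho_w = 1 and rho_b = 0, is sqrt(2/1.125) = 1.33. It is low because the single VE reading supplies 1 of the 1.125.

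**Step 2: rater differences, treated as random.** If raters differ with SD s in logits, their contribution to a four-rater mean has SD s/sqrt(4): 0.10 at s = 0.2 and 0.25 at s = 0.5. More children do not reduce it. Two simulations put this into coverage of nominal 95% intervals:

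| Simulation | Rater SD (logits) | SE ratio | Coverage |
|---|---|---|---|
| A | 0 | 0.81 to 1.18 | 98% to 91% |
| A | 0.2 | 2.45 | 58% |
| A | 0.5 | 6.6 | 20% |
| B | 0 | not tabulated | about 93% |
| B | 0.25 | 0.129/0.054 = 2.4 | about 62% |
| B | 0.5 | 0.221/0.054 = 4.1 | about 38% |

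A: risk-difference scale, 213 children (from Results), 20 teeth, 4 surfaces, VE prevalence about 7 to 11%, tooth (hence child) means removed, 150 replicates. B: logit scale, 213 children, 18 teeth, 4 surfaces, VE prevalence about 3%, tooth intercept only, 500 replicates. Neither includes zero inflation, so neither is an exact test of the planned model.

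**Step 3: individual level.** Each on-screen method gives 8 counts per child, and the paired model takes one. If they were averaged, the result would generally be a non-integer, which a Poisson model does not fit. It would also be more reliable than one examiner. By Spearman-Brown, an assumed single-reading reliability of 0.60 becomes 8(0.60)/(1 + 7(0.60)) = 4.8/5.2 = 0.923, raising the correlation with VE by sqrt(0.923/0.60) = 1.24, or 24%. At 0.80 it becomes 6.4/6.6 = 0.970, and the factor is sqrt(0.970/0.80) = 1.10. These are upper limits, because two readings by one rater share that rater's errors.

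**Step 4: Methods against Discussion.** The Discussion credits the approach with handling rater and timing when estimating method agreement. In the Methods those terms appear only in the comparison of the two on-screen methods.

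**The case against.** - **An article may leave data handling to a fuller plan.** True of the reduction step alone. But the Introduction says this article describes the statistical analysis plan, and it names the fixed effect, the clustering, the distribution and where rater and timing enter. The model it states lacks the terms.
- **On-screen rater and time have no VE counterpart**, and the Discussion discloses that VE was not repeated. This is a plausible reason for keeping them out of the VE models, and it stands as a caution on coding. Fixed rater effects alone would also not bring between-rater variance into the method interval.
- **Rater variation is not ignored overall.** Inter- and intrarater coefficients are planned for all on-screen examiners, and calibration must exceed a weighted kappa of 0.7. Both stand, but neither enters the VE comparison.
- **The Discussion may describe only what the approach can do.** That softens the mismatch; a reader will still take it as a statement about this study's estimates.
- **No test, margin or precision target hangs on these intervals**, and the Discussion concedes that the coefficients do not measure absolute agreement. This stands and limits the consequence.

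A reader might infer three stronger things that the document does not support. First, that 8 readings against one make intervals far too narrow: Step 1 caps this at 1.33 and allows the opposite. The severe figures need an assumed rater SD with raters treated as a random sample. Second, that clustering by child is dropped: the same paragraph names the individual level and the Discussion relies on it. Third, that counts will be averaged, or readings stacked: neither is stated.

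**Conclusion.** The point holds in a limited form. The VE-versus-on-screen models, as written, have no term pairing readings of the same surface and no rater or time term, and the Methods do not deliver what the Discussion claims. If readings are stacked, repetition alone leaves the true standard error anywhere from well below the model's to at most 1.33 times it, depending on correlations the document does not give. For conclusions beyond these four raters, the model's standard error would be too small if raters differ. The factors of 2.4 to 6.6 above illustrate assumed rater SDs of 0.2 to 0.5 logits and are not estimates for this study. The individual-level count is undefined for the on-screen methods, and averaging would cause the problems in Step 3. The 1:1 automated comparison is unaffected.

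**What to change.** 1. In the VE-versus-on-screen models, use random intercepts for child, tooth and surface, and include rater and time point for the on-screen readings. Because VE has no matching levels, code these as deviations within the on-screen readings, so that the method coefficient is an average over raters and times.
2. Report each rater's agreement with VE from the first reading. Add a pooled estimate that either carries between-rater variance or is stated to apply to these four raters only.
3. At individual level, pair VE with one rater's first reading at a time and summarise across the four raters.
4. Reconcile the Statistical Analysis section with the Discussion on where rater and timing are accounted for.

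Cost: wording and model terms only, with no new data. Intervals will be wider in some cases. A between-rater variance from four raters is poorly estimated, so the per-rater results are the main safeguard.

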#### Intraoral Scanning

Immediately following the VE, intraoral scanning took place using the TRIOS 4 scanner. This generation scanner has a high accuracy and fast acquisition time relative to other scanners on the market for complete arch scanning [32]. It also has specialized fluorescence technology built into its hardware which exposes teeth to 415-nm light during scanning. Light emitted from the teeth passes through a filter in the scanner (which filters out blue light) to be received by the scanner sensor. The fluorescence signal overlays onto the 3D models as green fluorescence and red fluorescence texture, aided by commercial software (TPM; version 2.3, Dental Desktop and TRIOS; 3Shape TRIOS A/S).

The clinical examiners were trained to use the 3Shape TRIOS software interface and intraoral scanning protocols. Before scanning, the dental lamp was switched off, and the window blinds were closed to limit external light during the scanning process as per manufacturer instructions [33]. Teeth were dried with gauze or cotton rolls, and the manufacturer-recommended scanning strategy was followed. The scanning procedure was considered adequate when the software had obtained sufficient information about tooth color and fluorescence for the region of interest. If the scan was incomplete, the reasons why the scanning procedure was inadequate were documented. The reasons for insufficient scan data included the scanner tip being too big to accommodate, gag reflex, and behavioral or developmental issues that limited cooperation with the scanning procedure. Both complete and incomplete 3D models were saved with the participant's unique identifier in the dental desktop software.

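### If VE-versus-scan disagreement clusters within children, the surface-level method coefficient gets too narrow an interval, because the planned model covers only clustering of caries level

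*Protocol article*

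**What the plan says.** The Statistical Analysis section of the protocol article sets out the hierarchy: "At the surface level, caries data naturally have 3 levels with surfaces clustered within a tooth, which are clustered within an individual". It then says that "we will use multilevel logistic regression to estimate method agreement while accounting for clustering for the tooth". Separate models compare VE with each alternative method. Method is the fixed effect, and "The coefficient estimates for the variable method will be used to indicate the level of agreement". The distribution is zero-inflated binomial.

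The sensitivity paragraph of the same section adds surface location and enamel defects, each with a method interaction; enamel defect is a yes/no variable per person. Rater and timing are added as fixed effects only for the colour-versus-fluorescence comparison.

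The Discussion gives the reason for the multilevel approach: "caries from the same individual are more correlated than those between individuals". It warns: "If this clustering is ignored, the estimated variance may be misleadingly small". It concludes: "We will use multilevel models that account for clustering". Nowhere does the article state a random method effect by child or a child-clustered variance.

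**The concern.** The clustering that the article argues from is clustering of caries: some children and some teeth have more of it. VE and the scan are compared on the same surfaces, so a child's caries level largely cancels out of the method contrast. The error of that contrast depends on something else, namely whether VE-minus-scan differences go together within a child.

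There are reasons to expect that they do. Each child had one scanning session, with its own drying, cooperation and completeness; the Intraoral Scanning section lists, among the reasons for insufficient scan data, "behavioral or developmental issues that limited cooperation with the scanning procedure". VE was done by two examiners, and the Discussion concedes that VE was not repeated by several raters over several time points. A difference between the VE examiners would then appear as a difference between children in VE minus scan.

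If so, the precision of the VE-versus-on-screen coefficients is overstated. The third objective is also at stake: the effect of enamel defects on agreement is judged by comparing children with children, exactly where unmodelled between-child variation does most harm.

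**Working it through.** The article gives no precision, power or variance figure for the method coefficient, so there is nothing of its own to reproduce. The check is a simulation under stated assumptions.

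**Model.** For each reading, logit P(caries) = a + u(child) + v(tooth) + w(surface) + (b + d(child)) × method, where d(child) has mean 0 and SD τ. The plan as printed has b but no d.

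**Inputs.** From the article: 213 children (the set with automated scoring completed, used here as the number of children). Assumed: 20 teeth × 4 surfaces = 80 surfaces per child; one VE and one on-screen reading per surface; intercept SDs of 1.5 (child) and 1.0 (tooth); surface SD 0 (prevalence about 2.6%) or 2 (about 6.1%); mean method effect 0; τ from 0 to 1.0. There were 500 replicates per setting, so the Monte Carlo error of a coverage near 0.95 is √(0.95 × 0.05/500) = 0.010. The fits used a plain logistic likelihood, not the zero-inflated one. Coverage is counted around the coefficient's own mean, so a shift in that mean is not scored as a failure.

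**Rough hand check.** With equal weights, child-specific effects add τ²/213 to the variance, and unequal weights add more. Taking the mean model SE with child, tooth and surface intercepts:
- τ = 0.5: 0.0559² + 0.25/213 = 0.00312 + 0.00117 = 0.0043, root 0.066. Simulated SD: 0.067.
- τ = 1.0: 0.0542² + 1/213 = 0.00294 + 0.00469 = 0.0076, root 0.087. Simulated SD: 0.089.

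**Results.** Each cell gives empirical SD ÷ mean model SE, then coverage of the nominal 95% interval.

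| τ | (a) Surface SD 0; tooth, or child + tooth intercepts | (b) Surface SD 2; surface intercept omitted | (c) Surface SD 2; child + tooth + surface intercepts | Model (c) with child-clustered SE: coverage |
|---|---|---|---|---|
| 0 | 1.01; 0.952 | 0.85; 0.986 | 0.98; 0.956 | 0.950 |
| 0.25 | 1.08; 0.922 | 0.90; 0.972 | 1.03; 0.938 | 0.954 |
| 0.5 | 1.25; 0.870 | 1.04; 0.948 | 1.20; 0.888 | 0.970 |
| 0.75 | 1.51; 0.794 | 1.24; 0.894 | 1.42; 0.856 | 0.960 |
| 1.0 | 1.81; about 0.73 | 1.45; 0.834 | 1.65; 0.774 | 0.962 |

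1. Adding a child intercept to the tooth intercept does not help. In (a) at τ = 0.5 the model SE is 0.0724 with either structure, against an empirical SD of 0.091.
2. Column (b) shows an opposing error. Ignoring that the two readings sit on one surface widens the interval, which offsets the narrowing up to about τ = 0.5.
3. A child-clustered sandwich variance gave coverage of 0.946 to 0.970 in every setting, including (b).

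**Enamel-defect interaction.** A second simulation assumed 213 children, 80 surfaces each, 30% of children with defects, prevalence about 7% and no true interaction (matched-pair log odds ratio, 2,000 runs). The nominal 95% interval excluded zero in 4.5%, 6.8%, 13%, 21% and 29% of runs at τ = 0, 0.25, 0.5, 0.75 and 1.0. With a child-clustered variance the figure was 4.8% to 5.6%.

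**Automated comparison.** With 8 occlusal surfaces per child, a 5% test of no method effect rejected in only 5% to 6% of runs.

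**The case against.** The strongest reply is that no document gives τ. At τ = 0 the interval is correct, and in the structure nearest the printed wording (tooth clustering, no surface term, surface effects present) coverage is nominal or conservative up to τ = 0.5. That stands. A reader might infer that the interval is simply too narrow, or that each surface is treated as independent evidence on agreement; the documents support neither. It does not make the plan safe, however. Two misspecifications that pull in opposite directions cancel only by accident, and coverage in (b) is 0.894 and 0.834 at τ = 0.75 and 1.0.

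Second, the article sets no significance level or decision rule for the coefficient, and the Discussion admits that the coefficients do not measure absolute agreement. So the false-positive rates above describe intervals under assumptions, not an error rate of this plan. That stands as well.

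Third, this is a condensed article, and a fuller plan might hold the missing term. This stands in part. But the Introduction says that the article describes the analysis plan, and the article commits to a structure and defends it by correlation of caries. Even its generous reading, with child and tooth intercepts, under-covers when disagreement clusters. A reader might go further and say that the Discussion promises protection against this problem; it speaks of correlated caries, not of correlated disagreement.

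Fourth, poor scans are partly removed by excluding surfaces with less than one-third visible, or obscured by plaque, calculus or debris. This weakens the scan-quality mechanism but leaves the VE-examiner one.

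Finally, the individual-level Bland-Altman and intraclass correlation analyses already use one count per child per method. They are unaffected, but they do not supply intervals for the surface-level coefficients.

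**Conclusion.** The point holds conditionally. The planned surface-level VE-versus-on-screen models allow for clustering of caries level, not for between-child variation in the VE-minus-scan difference. If that variation is material, the interval for the method coefficient is too narrow: coverage is about 0.89, 0.86 and 0.77 at assumed SDs of 0.5, 0.75 and 1.0 log-odds with child, tooth and surface intercepts. It is nominal at SD 0, and can be conservative at small SD if surface pairing is not modelled. The method-by-enamel-defect interaction carries the same risk.

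These sizes rest on the assumed variances, 80 surfaces per child, one on-screen reading per surface and a likelihood without zero inflation. The direction under material between-child variation does not depend on the exact values. The change is worth making because the variation is plausible and the remedy is cheap.

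**What to change.** In the Statistical Analysis section, for both the main surface-level models and the sensitivity models, state that confidence intervals for the method and method-interaction coefficients come from a bootstrap that resamples whole children, or from a child-clustered sandwich variance. The alternative is a random method effect by child together with child, tooth and surface intercepts; this was not fitted in the check above. Say also how the pairing of readings on one surface is handled. Resampling or clustering by child allows for that pairing too.

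The cost is a sentence or two of plan text and some computing time; no new data are needed. Intervals widen where disagreement clusters: in setting (c) the SE goes from 0.0559 to 0.0692 at τ = 0.5 (24%) and from 0.0542 to 0.0955 at τ = 1.0 (76%). At τ = 0 it is practically unchanged (0.0566 against 0.0562).
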